### Study visits and procedures

Within 3 months of completion of a Medeor clinical trial, the kidney transplant recipients who received a Medeor cellular immunotherapy product will begin annual study MDR-105-SAE visits at 12 months (with an allowed deviation of ± 1 month for scheduled annual visits).

Unscheduled study visits at the transplant center and at other health care delivery facilities may occur. Records from such visits would be obtained and reviewed for adequate safety reporting.

Extensions in study visit scheduling to accommodate non-working days will not be considered protocol deviations. Additionally, extensions in scheduling because of special circumstances, such as subject work issues, lack of transportation, and bad weather, if cleared in advance with the medical monitor, will also not be considered protocol deviations.

The schedule for clinical assessments is elucidated in Table 1 (below references).

**Table 1 Tab1:** Schedule of monitoring over the course of MDR-105-SAE

**Study visit year**	1		2	3	4	5	6	7
**Study visit number**	0	1	2	3	4	5	6	7
**Study visit window (months)**	+ 3	± 1	± 1	± 1	± 1	± 1	± 1	± 1
**Assessment**	**Screening**	**Post enrollment**						
Informed consent	⦁							
Confirm study eligibility criteria	⦁							
Demographics	⦁							
Baseline characteristics	⦁							
Medical history	⦁							
Prior/concomitant medication	⦁	⦁	⦁	⦁	⦁	⦁	⦁	⦁
Perform complete physical examination	⦁	⦁	⦁	⦁	⦁	⦁	⦁	⦁
Record vital signs	⦁	⦁	⦁	⦁	⦁	⦁	⦁	⦁
Record weight	⦁	⦁	⦁	⦁	⦁	⦁	⦁	⦁
Record height	⦁							
Hematology panel^a^		L	L	L	L	L	L	L
Comprehensive metabolic panel^a^		L	L	L	L	L	L	L
Urinalysis		L	L	L	L	L	L	L
Calcineurin inhibitor trough levels^b^		L	L	L	L	L	L	L
Mixed chimerism testing^c^		C	C	C	C	C	C	C
Record instances of acute rejection requiring treatment		⦁	⦁	⦁	⦁	⦁	⦁	⦁
Record instances of proteinuria		⦁	⦁	⦁	⦁	⦁	⦁	⦁
Kidney biopsy^d^		Only for cause						
Complete subject status form		⦁	⦁	⦁	⦁	⦁	⦁	⦁
Record all SAEs		⦁ (ongoing)						
Record AEs leading to study withdrawal		⦁ (as needed)						
Record history of hospitalizations since transplant		⦁	⦁	⦁	⦁	⦁	⦁	⦁
Record development of NODAT^e^		⦁	⦁	⦁	⦁	⦁	⦁	⦁
Record development of GVHD		⦁	⦁	⦁	⦁	⦁	⦁	⦁
Record instances of BK viremia development		⦁	⦁	⦁	⦁	⦁	⦁	⦁
Record instances of dnDSA		⦁	⦁	⦁	⦁	⦁	⦁	⦁
Record instances of cardiovascular events^f^		⦁	⦁	⦁	⦁	⦁	⦁	⦁
Record instances of opportunistic infection		⦁	⦁	⦁	⦁	⦁	⦁	⦁
Record instances of PTLD/other malignancies		⦁	⦁	⦁	⦁	⦁	⦁	⦁

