### Events of special interest

Clinically significant opportunistic infections (grade 3 Common Terminology Criteria for Adverse Events (CTCAE) or higher or meeting criteria of an SAE), all cancers other than PTLD, and cardiovascular events including revascularization procedures will be reported on dedicated electronic case report forms (eCRFs) for these events of special interest.Active surveillance for myelodysplastic syndrome (MDS)

Myelodysplastic syndromes (MDS) include a group of clonal myeloid neoplasms with presence of cytopenias due to ineffective hematopoiesis, abnormal blood, and marrow cell morphology [9]. These abnormal cells can undergo changes in clonality and progress to acute myeloid leukemia (AML). Some myelodysplastic syndromes have no known cause. Others are caused by exposure to cancer treatments, such as chemotherapy and radiation, or to toxic chemicals, such as tobacco, benzene, and pesticides, or to heavy metals, such as lead.

Active surveillance for MDS consists of full annual physical exam with medical history and evaluation for possible risk factors and CBC with platelets and differential. Additional tests such as vitamin B12 and folate may be required when results of CBC and physical exam are outside of normal parameters which often signal an underlying medical issue. MDS will not be reported as AEs, but as outcomes, and will be collected and reported on dedicated case report forms specifically designed to capture these events.(b)Reporting of pregnancy

Pregnancy is neither an AE nor an SAE, unless a complication relating to the pregnancy occurs. All reports of congenital abnormalities/birth defects are SAEs. Spontaneous miscarriages should also be reported and addressed as SAEs. Elective abortions without complications will not be considered AEs. However, all pregnancies occurring during this study (in subjects or female partners of subjects) are to be reported to the sponsor at the subsequent scheduled visit.

(c)Events to be reported as outcomes rather than adverse events

Rejection episodes, opportunistic infections, BK viremia, cardiovascular events, graft versus host disease (GvHD), post-transplant lymphoproliferative disorder (PTLD), MDS, and new-onset diabetes after transplantation, graft loss, and death are outcomes and will be reported on dedicated case report forms (CRFs) for these events. Causes of death should be reported as SAEs.(iv)Cardiovascular events

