### Statistics

#### Safety endpoints

Long-term safety will be assessed by summarizing incidence of serious adverse events (SAEs), AEs leading to study withdrawal, and hospitalization rates. Summary statistics will be presented by visit for laboratory data, including hematology, renal function, biochemistry, and vital signs. Adverse events will be classified for seriousness using standard regulatory criteria and for severity according to the National Cancer Institute—Common Terminology Criteria for Adverse Events (NCI-CTCAE) version 5 or higher grading scale whenever feasible.

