#### Outcomes of special interest

The number and proportion of subjects with biopsy-proven acute rejection (BPAR), de novo donor-specific antibody (dnDSA) (if applicable), BK viremia, opportunistic infection, post-transplant lymphoproliferative disorder (PTLD), myelodysplastic syndrome (MDS), new-onset diabetes after transplantation (NODAT), graft versus host disease (GvHD), cardiovascular (CV) events, and initiation of immunosuppression will be presented by visit and overall. Transplant kidney loss and subject death will also be summarized by visit and overall.

Outcomes of special interest noted above will not be reported as AEs, but rather as outcomes, and will be collected and reported on dedicated case report forms specifically designed to capture these events; this will include severity and seriousness assessments.

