## Discussion

The continued success of transplantation has been limited by adverse effects associated with immunosuppression. Immunosuppression is associated with increased risk for infections, malignancies, cardiovascular and metabolic disease (hypertension, hyperlipidemia, post-transplant diabetes mellitus), and allograft nephrotoxicity, and independently increases morbidity and mortality in transplant recipients [11]. In addition, chronic rejection, which can be immune or non-immune, can occur despite or because of use of immunosuppression, leading to progressive graft loss [12]. The generation of immune tolerance is the next frontier in transplantation to achieve continued durability of the graft without use of immunosuppression laden with adverse effects.

Various trials are now underway to assess the novel methodology of donor-derived CD34 + hematopoietic stem/progenitor cells and a specified dose of CD3 + T cells administered to recipients of kidney transplants post total lymphoid irradiation. While preliminary findings from these trials are extremely encouraging, long-term effects of this immune tolerance regimen are still largely unknown. Extension or “roll-over” studies are especially beneficial in the setting and can provide early evidence of outcomes, along signals of tolerability and safety issues [13].

The current study is unique given it combines multiple studies as a “master protocol,” a recent innovation in research methodology that can aid in evaluation of multiple therapies [14]. These studies have the advantage of utilizing existing infrastructure of trials being included in the master protocol and provide concurrent comparisons of therapies in different population groups [14].

The MDR-105-SAE is a long-term study that will provide long-term safety data in patients currently enrolled in various kidney transplant trials involving administration of immune tolerance regimes. It is imperative that these regimes be shown not only to be effective, but also be associated with long-term safety for the field of transplantation to take the next prodigious and essential step into the future.

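### All rejection episodes leave adverse event reporting, but only acute rejection is prompted for and tabulated, so biopsy-proven chronic rejection has no named row in the planned summaries

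*Protocol article*

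**What the plan says.** Three places in the article govern how rejection is recorded or reported.

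- **Events of special interest, item (c)**, headed "Events to be reported as outcomes rather than adverse events", begins its list with "Rejection episodes, opportunistic infections, BK viremia, cardiovascular events, graft versus host disease (GvHD") and sends these events to dedicated case report forms. Rejection is limited here neither to acute nor to biopsy-proven cases.
- **Table 1 (Study visits and procedures)** has one rejection row, marked at visits 1 to 7: "Record instances of acute rejection requiring treatment".
- **Statistics, Outcomes of special interest**, plans "The number and proportion of subjects with biopsy-proven acute rejection (BPAR") as its only rejection outcome, by visit and overall. It adds: "Outcomes of special interest noted above will not be reported as AEs, but rather as outcomes". It also says: "Transplant kidney loss and subject death will also be summarized by visit and overall".

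Safety endpoints covers serious adverse events (SAEs), adverse events (AEs) leading to withdrawal and hospitalization rates, and continues: "Summary statistics will be presented by visit for laboratory data, including hematology, renal function, biochemistry, and vital signs". Biopsies are for cause and are read by local pathology.

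The Discussion describes "chronic rejection, which can be immune or non-immune, can occur despite or because of use of immunosuppression, leading to progressive graft loss". The Background lists rejection, with no acute limit, alongside graft dysfunction or loss as something that needs monitoring.

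**The concern.** The category taken out of adverse event reporting is wider than the category prompted for at visits, and wider than the category tabulated. Chronic rejection sits in the difference.

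This matters because of when the study observes people. Follow-up starts after the parent study and runs for up to 84 further months, and the initial parent trial uses progressive tapering of immunosuppression. The Background itself cites two late rejections, at 44 and 60 months, in an earlier single-center study (type not stated). Someone reading the final report to learn how many recipients developed biopsy-proven chronic rejection would find no line that answers the question.

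**Working it through.** No arithmetic applies. The article states no sample size, event count or rate, and the point is about which events the planned outcomes cover. The check is to set the three definitions side by side and follow one case through them.

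| Place | Role | Limited to acute? | Biopsy required? | Treatment required? |
|---|---|---|---|---|
| Events of special interest, item (c) | Sends the event to an outcome form instead of AE reporting | No | No | No |
| Table 1 | Visit prompt | Yes | No | Yes |
| Outcomes of special interest | Number and proportion tabulated | Yes | Yes | No |

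**Test case.** A for-cause biopsy is read locally as chronic rejection with no acute rejection. It fails the second and third rows because it is not acute. A chronic active reading falls in the same gap unless the form or the reader counts it as acute, which the article does not settle.

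**Reading A: item (c) includes chronic rejection.** The event goes on the dedicated form and is not reported as an AE. Outcomes of special interest has no line for it. The data may exist, but no summary of them is planned.

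**Reading B: item (c) means acute rejection only.** Chronic rejection is then an ordinary AE. The study records SAEs and AEs leading to withdrawal. A serious case would enter the SAE tables under its coded term, and a case leading to withdrawal would enter that summary. A case that is neither is counted nowhere as rejection.

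Under both readings, a non-serious biopsy-proven chronic rejection that does not lead to withdrawal has no row in any planned summary. Under neither reading is chronic rejection named as an outcome.

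**Do the other summaries identify it?**

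- Kidney loss is the end result. The Discussion calls that loss progressive, so it is a late marker.
- De novo donor-specific antibody is a separate finding, not a biopsy diagnosis.
- Renal function by visit, yearly eGFR and recorded proteinuria show decline from any cause.
- Initiation of immunosuppression and hospitalization rates reflect decisions or admissions for any reason.

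These would register some consequences of chronic rejection, but none identifies it.

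**The case against.** The strongest reply has four parts.

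1. **Chronic rejection may well be collected.** Item (c) puts unrestricted rejection episodes on a dedicated form. A reader might infer from Table 1 that only acute rejection is collected. The article does not support that, because the form may capture every type. This part of the reply stands in full.
2. **Related outcomes are summarised.** Kidney loss, de novo donor-specific antibody, initiation of immunosuppression and renal function are all planned, so graft decline would show before graft loss. This stands, and it rules out saying that chronic rejection leaves no trace in any planned outcome. It does not supply a count of chronic rejection.
3. **The acute rejection proportion is not biased.** A reader might infer that it is biased low. It is a named, narrower outcome, and leaving chronic rejection out of it does not distort it. The article plans no any-rejection proportion and no rejection-free category that could be wrong. This stands.
4. **The article condenses a fuller protocol, and the Discussion is background.** Whether the form has a type field, and whether kidney loss is tabulated by cause, may be settled in documents not shown. This stands for those details, so kidney loss by cause is not part of the point. It does not remove the mismatch, because the article itself fixes what leaves AE reporting, what the visit row prompts for and what is tabulated, and the three differ.

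**Conclusion.** The point holds as a gap in outcome coverage. As written, the plan removes a broad rejection category from AE reporting and tabulates a narrower one, so biopsy-proven chronic rejection has no named row in a safety study lasting up to 7 years. The article's own Background and Discussion make rejection and progressive graft loss central to that study.

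Its size cannot be put in numbers. The article gives neither the number of subjects nor a chronic rejection rate, and any count would follow wholly from assumed inputs. The conclusion rests only on the wording of the three places and assumes they are applied as written. The full protocol, analysis plan or forms could narrow the gap if they already record rejection type and tabulate it.

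This is a cheap improvement to a descriptive study and does not invalidate any planned estimate.

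**What to change.** Reconcile Events of special interest item (c), Table 1 and Outcomes of special interest:

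- In item (c), state that the rejection form covers all rejection and records its type (acute, chronic or chronic active) and whether it was biopsy-proven.
- Reword the Table 1 row so that it prompts for all rejection with its type. Whether treatment was given can stay as a field on the form.
- In Outcomes of special interest, keep biopsy-proven acute rejection and add two lines: biopsy-proven chronic or chronic active rejection, and any biopsy-proven rejection. Present each by visit and overall, like the existing outcomes.

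The same edit would settle the separate difference between treated acute rejection in Table 1 and biopsy-proven acute rejection in the statistics section.

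The cost is form wording and two extra table lines. The for-cause biopsies and local pathology reads are already planned, so no new procedure or reader is needed and clinical management is unchanged. The any-rejection proportion may be higher than the acute proportion alone, so the report should show the lines together. The wording is best settled early, because a rejection type that is not recorded at the time may be hard to recover years later.

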### Monitoring and reporting serious adverse events only

All subjects will be monitored closely for SAEs during study participation. Subjects who discontinue prematurely from the study will be encouraged to return for assessment of safety. Follow-up safety information may also be obtained directly from a subject’s physician with source document support whenever applicable (e.g., biopsy results) or from medical records, laboratory reports, and imaging reports.

Whenever possible, symptoms should be grouped as a single syndrome or diagnosis. The investigator should specify the duration (start and end dates) or if the event is ongoing, the severity grade, other medication or therapies have been taken (concomitant medication/non-drug therapy), outcome, and his/her opinion as to whether there is a reasonable possibility that the SAE was caused by the previous study treatment.

In the event of an SAE, the investigator should follow up with the outcome until the clinical recovery is complete and laboratory results have returned to normal or until progression has been stabilized.

The investigator must provide the sponsor appropriate information concerning any findings suggesting significant hazards, contraindications, side effects, or precautions pertinent to the safety of the study treatment. Direct contact information for the Study Medical Monitor will be provided to the institution at time of institutional review.

All SAEs must be reported to the Sponsor within 24 h of the first awareness of the event. The Investigator must complete, sign and date the SAE pages, verify the accuracy of the information recorded on the SAE pages with the corresponding source documents, and send to sponsor:The SAEs will be reported to the sponsor by completing an SAE Report Form. All sections on the form are to be completed. Information that is not available at the time of initial reporting should be submitted as a follow-up. The date of receipt of an initial SAE Report Form will be considered as day 0 for the purpose of determining the time for regulatory reporting of an expedited event and timelines of further study-related activities.The copy of all examinations carried out and the dates on which these examinations were performed will be attached. For laboratory results, the laboratory normal ranges will be included.

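### Non-fatal serious outcomes of special interest are left out of SAE incidence, and no stated rule sends them into the 24-hour sponsor and IRB pathway

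*Protocol article*

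**What the plan says.** Under Safety endpoints, the protocol article states: "Long-term safety will be assessed by summarizing incidence of serious adverse events (SAEs), AEs leading to study withdrawal, and hospitalization rates". The Abstract and Assessment of safety name the same three measures.

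Under Definition of serious adverse event (SAE), an SAE is an adverse event with one of a list of results, including death, threat to life and inpatient admission.

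Two places then move a group of events out of adverse event reporting:

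- Events of special interest, item (c), lists rejection, opportunistic infection, BK viremia, cardiovascular events, GvHD, PTLD and MDS, and ends: "new-onset diabetes after transplantation, graft loss, and death are outcomes and will be reported on dedicated case report forms (CRFs) for these events". It adds: "Causes of death should be reported as SAEs". On MDS the same section also says: "MDS will not be reported as AEs, but as outcomes".
- Outcomes of special interest, in the Statistics section, says: "Outcomes of special interest noted above will not be reported as AEs, but rather as outcomes". Of the dedicated forms it says: "this will include severity and seriousness assessments". It also commits to counts and proportions for each outcome, by visit and overall, with graft loss and death summarized likewise.

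Expedited reporting is set out under Monitoring and reporting serious adverse events only. The sponsor rule begins "All SAEs must be reported to the Sponsor within" and sets 24 hours from first awareness. The duty to notify the IRB is likewise worded for SAEs.

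**The concern.** This is a safety extension with no other purpose, and SAE incidence is the first measure it names. The Background singles out rejection, graft dysfunction or loss, GvHD and opportunistic infection as events that must be watched, and the protocol sets up active surveillance for MDS. If the non-fatal serious cases of these events cannot be SAEs, the SAE percentage describes only the remaining serious events. A reader who takes it as the share of subjects with a serious event will read it as too low.

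The second consequence concerns reporting. If the 24-hour report and the IRB notice depend on the label SAE, a serious but non-fatal GvHD, PTLD or MDS case has no stated clock. The protocol nevertheless promises continuous monitoring for safety signals and is open to future studies of these products.

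**Working it through.** The article gives no sample size, event rate or target for this study, so there is no planned figure to reproduce. The check sets the definitions side by side.

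1. **Adverse event.** The definition covers any unfavourable, unintended diagnosis that is new or worse during the study. On its face this includes GvHD, PTLD, MDS, rejection and myocardial infarction.
2. **SAE.** The definition requires an adverse event plus a seriousness criterion. An event that is not reported as an adverse event therefore cannot be counted as an SAE.
3. **Classification.** The Statistics section takes the listed outcomes out of adverse event reporting, and item (c) of Events of special interest sends them to dedicated forms.
4. **Non-fatal serious outcome.** From steps 2 and 3, its contribution to SAE incidence is 0.
5. **Fatal outcome.** The cause of death is to be reported as an SAE, so it counts and the 24-hour rule applies. The Statistics section does not repeat this exception.
6. **Reporting.** The 24-hour and IRB rules name SAEs. Outcome forms fall under Case report form completion, which asks for entry as soon as possible and sets no hour limit. Table 1 marks SAE recording as ongoing but places GvHD, PTLD, MDS, opportunistic infection and cardiovascular events at the annual visits. The text neither exempts serious outcomes from expedited reporting nor routes them into it.
7. **Use of the seriousness assessment.** It is collected on the outcome forms, but no table, endpoint or reporting rule refers to it.

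Tracing one non-fatal admission for GvHD through the planned summaries:

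| Summary | Does it count? |
|---|---|
| SAE incidence | No, read literally |
| Hospitalization rates | It may; the measure is not limited to adverse events |
| GvHD table, by visit and overall | Yes, whether serious or not |
| Subjects with any serious event | No such summary is stated |

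**Size.** Let *s* be the proportion of subjects with an SAE as defined, and *o* the proportion with a serious outcome of special interest that is not counted as an SAE. The proportion with either lies between max(*s*, *o*) and min(1, *s* + *o*). The document gives neither *s* nor *o*, nor how far they overlap.

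To show how much depends on overlap, take *s* = 0.40 and *o* = 0.30, both purely assumed:

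- complete overlap: 0.40, a gap of 0 percentage points;
- independence: 1 − (1 − 0.40)(1 − 0.30) = 1 − 0.60 × 0.70 = 0.58, a gap of 18 points;
- no overlap: 0.40 + 0.30 = 0.70, a gap of 30 points.

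Even with both proportions fixed, the gap runs from 0 to 30 points. Separate tables therefore cannot supply the combined figure; it needs subject-level linkage.

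**The case against.** The strongest reply is that nothing is hidden. Each outcome has its own table in the same Statistics section, which tells a reader more than a pooled SAE percentage. Hospitalization is a co-listed headline measure and Table 1 records it at every follow-up visit, so an admission for GvHD or infarction can appear there. The study is observational and the article describes no comparator arm, so no treatment contrast is biased. This stands, and it rules out saying that the main harms are missing from the safety analysis. It does not supply an incidence of any serious event per subject, and it does not change what the SAE percentage leaves out.

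A second reply is that death is not excluded. That is right. A reader might infer from "graft loss, and death are outcomes and will be reported on dedicated case report forms (CRFs) for these events" that fatal events also drop out, but the sentence on causes of death brings them back, and the two can be read together: death is the outcome and its cause is the event. What remains is that the Statistics section is silent on the exception.

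A third reply is that missed expedited reporting is an inference. No exemption is stated. The text accepts that an opportunistic infection can meet SAE criteria, investigators must pass on findings that suggest significant hazards, and form routing may be set out in the full protocol or the Manual of Procedures, which are not shown. This also stands in part: one cannot say that every such case will miss the 24-hour report. But none of these passages sets a clock, and the article does fix the classification on which the clock depends.

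**Conclusion.** The point holds in a limited form. As written, non-fatal outcomes of special interest that meet the seriousness criteria contribute nothing to SAE incidence, and no stated rule gives them a 24-hour sponsor report or an IRB notice. This rests on a literal reading of the SAE definition together with the two classification passages. The harms are absent from SAE incidence and from any per-subject serious-event incidence; they are present in the outcome tables and possibly in hospitalization rates.

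The understatement cannot be calculated from the document. A reader might be tempted to quote a percentage, but that would need event rates and an overlap assumption that the protocol does not provide. The case for change does not depend on a figure: in a study that exists to describe long-term safety, the first-named measure should not leave open which serious events it counts, and sites should not have to guess which of them are expedited.

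**What to change.** 1. Under Safety endpoints, add the incidence of any SAE or any outcome assessed as serious on its dedicated form, counted once per subject, with SAE-only and outcome-only incidence shown as components.
2. In item (c) of Events of special interest, and under Monitoring and reporting serious adverse events only, state that an outcome meeting the SAE seriousness criteria also follows the 24-hour sponsor and IRB reporting pathway.
3. Reconcile the SAE definition, item (c) and the Statistics section on death, so that the cause-of-death exception appears wherever the classification is stated. The same edit can settle the status of cancers other than PTLD, which have a dedicated form but are in neither outcome list.

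The cost is protocol wording, one more table and some additional SAE forms. The seriousness assessment is already collected. The combined rate cannot be lower than the SAE-only rate, so the headline figure may look less favourable; showing the components keeps the SAE-only figure visible.
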